##### iii) Fagerström Nicotine Dependence Scale (FNDS)

A short 6-item instrument used for assessing the intensity of physical nicotine addiction [77].

##### iv) DSM-5 alcohol use disorder

A 12-item questionnaire assessing alcohol use based on the DSM-5 criteria [4].

##### v) Cannabis Use Disorder Identification Test – Revised (CUDIT-R)

A cannabis misuse screening tool containing 8 items, two from each of the domains of consumption, cannabis problems (abuse), dependence, and psychological features [78].

##### vi) DSM-5 substance abuse disorder

An 11-item questionnaire assessing substance use disorders based on the DSM-5 [4].

##### vii) NIDA-Modified Alcohol, Smoking, and Substance Involvement Screening Test (NM-ASSIST)

A 15-item measure adapted from the World Health Organization (WHO) Alcohol, Smoking and Substance Involvement Screening Test, used to assess prescription medicine and illicit substance use in adults age 18 and older [79].

#### Trauma-related risk factors

Early Life Stress Questionnaire (ELSQ): A 19-item questionnaire used to retrospectively assess exposure to early life stress, by ascertaining whether the participant had experienced physical, emotional, or sexual abuse as well as other traumatic experiences such as sustained bullying, poverty, divorce, illness, or domestic violence. If a stressor was present, the participant identified age of onset (0-12 years of age) [80].

#### Real world function and coping

##### i) Brief COPE

A multidimensional coping inventory to assess the different ways in which people respond to stress [81].

##### ii) Emotion Regulation Questionnaire (ERQ)

A 10-item questionnaire designed to assess individual differences in the habitual use of two emotion regulation strategies: cognitive reappraisal and expressive suppression [82].

##### iii) Social Functioning and Adjustment Scale (SOFAS)

The SOFAS is a derivative of the Global Adjustment Scale and reflects the individual’s level of social and occupational functioning, rated on a scale from between 0 and 100 [83].

##### iv) World Health Organization Quality of Life (WHOQOL) scale

This is a 30-item scale that assesses the psychological, general health, physical and environmental aspects of quality of self-reported quality of life, each assessed out of 100 [84].

##### v) Satisfaction With Life Scale (SWLS)

A short, 5-item instrument designed to measure global cognitive judgments of satisfaction with one’s life [85].

##### vi) Health Productivity Questionnaire (HPQ)

This is a 14-item scale that assesses productivity at work, and relative and absolute levels of absenteeism from work as well as presenteeism (being at work, but unproductive due to the effects of anxiety and depressive symptoms [86].

#### Acquisition and quantification

Each self-report measure is presented in a computerized format. Individual item scores are recorded and then summed automatically according to symptom cluster and scale definitions. The only exception to automated scoring is the SOFAS, which is rated by study coordinators.

### Follow-up outcome measures

At 12-week follow-up, we assess change in/stability of symptoms using the PSWQ, DASS and MASQ, HPQ and WHOQoL.

### Translational outcomes: toward a precision mental health protocol

Participants are offered the opportunity to partake in a brief feedback session (i.e., 30 min) with the study principal investigator, key clinical personnel and their current therapist. The feedback is based on self-report measures such as mood and anxiety symptoms, social and occupational functioning, and behavioral tests of emotion and cognition. A brief clinical summary of the participant’s history is provided to the investigator as contextual information. The investigator discusses the participant’s profile on the measures, describes relevant test performance, and gives recommendations for how this information could be applied to treatment. Anxiety and depression are examined from an RDoC perspective incorporating such dimensions as threat reactivity, threat regulation and cognitive performance; the participant is offered an overview of their experience based on a neural circuitry perspective. The participant and their therapist are given the opportunity to ask questions regarding current symptomatology as related to the neuroimaging and behavioral data. At the conclusion of the feedback session, the investigator exits while the participant and therapist consider the information received. The ultimate goal is to collaborate on incorporating the feedback into the current treatment plan. Treatment outcomes such as symptom reduction and therapy retention will be examined for participants who receive the feedback.

### Data management

All data are de-identified using participant numbers and no session number is identified. Follow-up data is distinguished from baseline visit data with timestamps and distinct variable names.

Source documents will be archived for 7 years beyond study completion, or in accordance with IRB regulations, whichever is longest.

Neuroimaging data are managed using the quality control and data management infrastructure at the Stanford Center for Neurobiological Imaging (CNI). At CNI, the Neurobiological Image Management System (NIMS) has been in use for the past four years. The current version of the software supports standardized format (DICOM) files. NIMS was designed to address key issues in order support the principles of reproducible research by i) enabling data sharing in way that is consistent with current norms in the field of neuroscience and ii) combining imaging data and metadata about subjects in a searchable database system.

For the computerized behavioral tests, the computer registers each response and writes these with time stamps to a log file. For the questionnaires, each self-reported response entered by participants is logged. These data are stored in a PHI-protected database and then integrated with the neuroimaging data.

In accord with the requirements of the project funding award, the data will be shared via the NIMH RDoC database, RDoC-db.

### Statistical analysis

The statistical analysis plan is designed to test specific working hypotheses relevant to each of the primary aims of the study:We will use both a priori approaches to group participants into “high” versus “low” subgroups on each imaging circuit measure, and their combination. We will also use data-derived techniques such as cluster and factor analysis to complement these a priori approaches.We will use General Linear Models (GLMs) to compare “high” versus “low” brain circuit-derived subgroups and data-derived clusters on symptom profiles. In correlational models we will assess the relationships between brain imaging dimensions and specific symptom profiles.We will use GLMs to compare brain imaging-derived subgroups/clusters on behavioral performance. We will also test associations between behavior, imaging and symptoms using correlational and mediator/moderator models.We will use GLMs to compare brain imaging-derived subgroups/clusters on real-world function. We will also test associations between function, imaging, behavior and symptoms using correlational and mediator/moderator models.

The statistical analysis plan also addresses the secondary aims of the study:4.Repeated-measures GLMs, reliability and regression models will be used to assess change (or stability) in symptoms and function at follow-up and to test if imaging at baseline predicts profiles of symptoms and function after 12 weeks.

We will use multiple methods to integrate the data under each aim.

As noted above we will use mediator and moderator approaches to model the relationship between imaging, symptoms, behavior and/or function at baseline and over time.

Second, we will employ multiple methods for implementing data reduction and pattern discovery, depending on the dimensionality and distributions of data domains. For example, we will employ model-based sparse factor analysis [87], a method that has been developed and successfully employed on functional neuroimaging data. We will do so hierarchically, to find simple structure within each domain separately, and then across domains, using Bayesian Belief Nets [88] to obtain directed relationships. We will also examine associations between domains using modern variable selection techniques such as the Elastic Net [89], a combined regression and variable selection methodology that is capable of handling large numbers of correlated explanatory variables. Finally, we will use techniques such as canonical correlation analysis to determine linear combinations of variables in given domains (e.g., neuroimaging) that maximally relate to variables in other domains (e.g., behavioral or symptoms).

### Power calculation

Power is estimated for GLMs assuming a small effect size of Cohen’s f^2^ = 0.10. With 160 subjects (after drop-out and exclusions) and with moderately correlated predictors (average r = .5) after multiple testing adjustments, we have well over 80 % power to detect effect with family-wise corrected alpha level of p < .05 [90].

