### Recruitment

We aim to enroll 160 participants who comprise a clinical-community sample. Enrollment commenced in August 2013, and we anticipate enrollment for baseline assessments will be completed in 2017.

We are enrolling patients from the Gronowski Center (GC), a community mental health training clinic, and individuals from the immediate surrounding community. The target of 160 ensures sufficient statistical power and coverage of the spectrum of anxiety and associated mood symptoms. Our power calculation is designed to test for an anticipated regression model with a medium effect size; approximately .5 (or f^2^ = .0625). With an alpha level of .05, a power level of .80, two primary predictors (our R0Is) and four additional predictors (behavioral and questionnaire measures) we require at least 158 participants. We have anticipated screening at least 3 times the target number in order to achieve a total enrolled sample of 160.

We are not using psychiatric diagnosis as inclusion criteria. We include participants spanning the dimension from healthy through sufficiently severe to meet diagnostic criteria.

To demonstrate the spread of coverage from our recruitment strategy, we record diagnosis (or absence of diagnosis), but do not use this information for primary analyses. Based on prevalence data from the existing GC records, we have anticipated the following spectrum of diagnoses: social anxiety disorder (6 %), generalized anxiety disorder (13 %), panic disorder (3 %), agoraphobia or specific phobia (1 %), post-traumatic stress disorder (8 %), obsessive compulsive disorder (4 %), major depressive disorder (26 %), persistent depressive disorder (dysthymia) (12 %), bipolar disorder 1 (5 %), other specified or unspecified depression or anxiety (5 %).

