### 1. Clinical interview, medical history and demographics

At baseline the MINI-Plus [44] is used to assess DSM-IV criteria for anxiety and mood disorder and to confirm exclusions due to psychosis and/or clinically significant mania. To ensure currency we also apply DSM-5 criteria to the information gathered at interview. Research personnel also gather comprehensive information on past and current medical history and additional sociodemographic data.

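### The same 160 is given both as the number enrolled and as the number left after drop-out and exclusions, and the Recruitment calculation leaves room to lose only two participants

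*Protocol article*

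**What the plan says.** The protocol article has two power statements.

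- **Recruitment.** The target is an enrolment figure: "We aim to enroll 160 participants who comprise a clinical-community sample". The screening allowance ends at the same point: "We have anticipated screening at least 3 times the target number in order to achieve a total enrolled sample of 160". The calculation takes f² = 0.0625, described as a medium effect, with these settings: "With an alpha level of .05, a power level of .80, two primary predictors (our R0Is) and four additional predictors". It concludes: "we require at least 158 participants".
- **Power calculation.** The effect is different: "Power is estimated for GLMs assuming a small effect size of Cohen’s f^2^ = 0.10". The sample is described as what remains after losses: "With 160 subjects (after drop-out and exclusions) and with moderately correlated predictors". With a family-wise alpha of .05 after adjustment for multiple testing, power is put comfortably above 80%. The number of tests is not given.

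The article states no loss rate and no enrolment figure above 160. It does describe where losses can arise. Quality control diagnostics are run on each fMRI time series (Functional scans), and symptoms and function are re-assessed at 12 weeks (Methods and design; Follow-up outcome measures). The baseline interview is also used "to confirm exclusions due to psychosis and/or clinically significant mania".

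**The concern.** One number cannot be both the intake and the count after losses unless losses are zero. The three-fold screening allowance does not resolve this, because it covers the step from screened to enrolled and stops at 160 enrolled.

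A reader therefore cannot tell which sample size supports which power statement. If 160 is the intake, the evaluable sample is smaller than the Power calculation section assumes, and the Recruitment section's requirement of 158 has almost no slack. The two objectives are also exposed differently. The primary objectives can be analysed from baseline data and lose participants mainly through unusable scans. The secondary objective needs 12-week data as well, so drop-out comes on top.

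**Working it through.** **Inputs from the article.** Recruitment: f² = 0.0625, alpha .05, power .80, 2 primary predictors plus 4 others (6 in the model), at least 158 required, 160 enrolled. Power calculation: f² = 0.10, family-wise alpha .05, 160 after losses.

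**Assumptions.** Loss rates of 5, 10, 15 and 20%. For the Power calculation section, the same test of 2 out of 6 predictors, and Bonferroni alphas chosen for illustration. The article states none of these.

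**Formula.** Power of the F test for u = 2 tested predictors in a model with k = 6: v = n − k − 1 = n − 7, noncentrality λ = f² × n, power = P(F′(u, v, λ) > F crit), where F crit is the upper-alpha point of F(u, v).

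**Step 1: reproduce the 158.** At n = 158, v = 151, λ = 0.0625 × 158 = 9.875 and F crit = 3.056, so power is 80.2%. At n = 157 it is 79.9%. The smallest n reaching 80% is therefore 158, as stated. (With λ = f² × (u + v + 1) the requirement would be 162. The stated figure matches the first convention, which is used below.)

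**Step 2: the margin.** 160 − 158 = 2 participants, and 2/160 = 1.25%.

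**Step 3: power after losses, n = 160 × (1 − loss).**

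| Assumed loss | n | Recruitment (f² = 0.0625, alpha .05) | Power calculation (f² = 0.10, alpha .05 unadjusted) | Power calculation (f² = 0.10, assumed alpha .0125) |
|---|---|---|---|---|
| none | 160 | 80.7% | 95.3% | 87.1% |
| 5% | 152 | 78.5% | 94.2% | 84.8% |
| 10% | 144 | 76.1% | 93.0% | 82.3% |
| 15% | 136 | 73.5% | 91.4% | 79.4% |
| 20% | 128 | 70.6% | 89.6% | 76.1% |

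**Step 4: how far the Power calculation claim depends on multiplicity.** For f² = 0.10 and the same test, 80% power needs 100 participants at alpha .05, 138 at .0125, 149 at .05/6 and 162 at .005. At the last of these, power is 79.3% even with all 160.

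**Step 5: detectable effect.** Solving for the f² that gives 80% power at alpha .05: 0.061 at n = 160, 0.068 at n = 144 and 0.077 at n = 128.

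**Step 6: enrolment implied if 160 really were the number after losses.** 160/(1 − loss), rounded up: 169, 178, 189 and 200 at 5, 10, 15 and 20%.

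**The case against.** The strongest reply is that the two sections are separate calculations. The 158 and the 80% belong to Recruitment. The Power calculation section uses f² = 0.10 and does not rely on 158. A reader might infer that losing a third participant breaks the power claimed there, or that the stated power holds for no analysis in the study. The documents support neither. At n = 157 and f² = 0.10, power is 94.9% unadjusted and 86.3% at an assumed alpha of .0125. Whether larger losses bring it below 80% turns on a number of tests that is not given. This part of the objection stands.

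Three further points limit the finding.

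- Even under the Recruitment calculation the third loss costs almost nothing (79.9%). The shortfall becomes material only at loss rates that are assumed here, so it cannot be said that the evaluable number will fall to any particular value.
- The article does not define when a person counts as enrolled. Exclusions confirmed at the baseline interview or on-site may precede enrolment and be absorbed by the screening allowance. Unusable scans and 12-week drop-out are the clear losses after enrolment.
- Drop-out by week 12 does not affect analyses of the primary objectives that use baseline data alone.

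None of this removes the contradiction over what 160 counts. Nor is it a detail left to an analysis plan, since both figures stand in the article.

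**Conclusion.** The point holds in a limited form. The article defines 160 in two incompatible ways, and nothing else in it reconciles them. Under the Recruitment calculation, which reproduces, the allowance for loss is two participants, and power falls from 80.7% at 160 to between 78.5% and 70.6% at assumed losses of 5 to 20%.

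The claim in the Power calculation section is not shown to be wrong. On an assumed test of 2 out of 6 predictors it is robust to loss without adjustment (95% at 160, 90% at 128). At an assumed alpha of .0125 it is sensitive to loss (87% at 160, 82% at 144, 76% at 128). It cannot be verified as written, because neither the number of tests nor the true evaluable sample is stated.

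The defect lies in the sample-size justification. It changes no analysis or estimate.

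**What to change.** 1. In Power calculation, delete the parenthesis on drop-out and exclusions, and keep 160 as the number enrolled throughout.
2. State the expected loss, and give power at the expected evaluable number for (a) usable baseline imaging (primary objectives) and (b) usable imaging plus 12-week data (secondary objective).
3. Keep each restatement on its own section's terms. In Recruitment use f² = 0.0625 and alpha .05, for example: n = 144 gives 76% power and a detectable f² of 0.068; n = 128 gives 71% and 0.077. In Power calculation use f² = 0.10 and the adjusted alpha actually planned, stating the number of tests. The Recruitment figures should not be carried into the Power calculation section, which rests on a different effect size and alpha.
4. Reconcile the two effect sizes. At present 0.0625 is called medium and the larger 0.10 is called small.

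The cost is a change of wording and a slightly less favourable stated power. No added enrolment is needed.

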## Discussion

The project aligns tightly with the goals and units of measurement defined by RDoC [10], to advance a neurobiologically informed understanding of mental disorders. Currently our understanding of the brain basis of anxiety and mood disorders is limited, especially at the individual patient level. To our knowledge, no previous study has characterized types of brain circuit dysfunctions across disorders and then evaluated how these dysfunctions relate to specific symptom profiles, behaviors and real-world functioning. Defining these types of dysfunction and relationships in a cohesive way will provide a foundation for ultimately tailoring interventions to individual needs.

We suggest that, to move forward in understanding the mechanisms of anxiety and depression and potentially improve quality of life, a shift is required to understanding the brain circuit domains linked to observed symptoms, behavior and function. Given that anxiety and depression are so prevalent [1, 2] generate significant disability [3] and we do not yet have biomarkers to help guide treatment decisions in clinical settings this study addresses an important public health need to understand these disorders from a neurobiological rather than diagnostic point of view -- in order to better explain the mechanisms by which dysfunction occurs and to better treat these disorders.

Strengths and innovation of this project include the use of mechanistically delineated paradigms for probing brain circuits and behavior such that brain-based constructs can be interpreted in the context of their behavioral expression as well as symptoms, the grounding in a conceptual model that goes beyond simply emotion processing to cognition and real world function, the use of well-established standardized assessments, and the clinical partnership that ensures recruitment of a sample representative of the community of people with anxiety and mood disorders.

## Limitations and challenges

We are conscious that recruitment of participants from community settings is a complex undertaking, which requires us to consider the clinical priorities of therapists and center supervisors. There is also a need to ensure a smooth flow for testing visits and to minimize participant burden. We have optimized the flow by using standardized assessments that minimize assessment time and by establishing a participant-friendly environment for the assessments. We also ensure that one research coordinator maintains contact with each participant to individualize the experience and to maximize retention in the study. Data collection will generate a large volume of data, and we have sought to address data management issues by establishing an efficient server infrastructure.

Despite these challenges, the project is expected to have an immediate impact on delineating the brain circuits and behavior that define cohesive constructs within the spectrum of anxiety and mood disorders, resulting in a new approach to diagnoses of anxiety and mood and provide a foundation for future tailoring of treatments to individual needs.
